### Recruitment

Participants are recruited through a combination of community-based and digital strategies, including caregiver and young adult support groups, TGD-serving organizations, community events, and targeted listservs and newsletters. The study team also leverages personal and professional networks to connect with LGBTQIA+ (lesbian, gay, bisexual, transgender, queer, questioning, intersex, asexual) organizations and individuals.

A key goal of the study is to ensure that at least 50% of enrolled participants are people of color. To support this, we implemented the following targeted recruitment strategies. (1) Community partnerships and outreach: We collaborate with community-based organizations, clinics, and advocacy groups that specifically serve communities of color to raise awareness about the study and encourage participation. (2) Culturally responsive research team: Our team includes trained researchers who have skillsets and experience working with study participants from diverse racial, ethnic, and lived experience backgrounds to help build trust, rapport, and cultural humility in our engagement with communities of from various cultural backgrounds. (3) Diverse research team: Our team includes researchers from diverse racial, ethnic, and lived experience backgrounds to help build trust, rapport, and cultural humility in our engagement with communities of color. (4) Ongoing monitoring and adaptation: We continuously monitor participant demographics and adapt recruitment strategies as needed to meet our diversity and inclusion benchmarks.

### Study Procedures

Potential participants are screened for eligibility online using a study-specific REDCap (Research Electronic Data Capture) screener. Those who appear preliminarily eligible are directed to a contact information form where they provide their name, email, phone number, and preferred method of contact. Study staff then follow up using the contact information provided to schedule an enrollment visit to confirm study eligibility and obtain informed consent. For individuals screened by phone, staff enter the contact information directly into REDCap during the call and schedule the enrollment visit in real time.

All enrollment visits are conducted remotely via a HIPAA (Health Insurance Portability and Accountability Act)-compliant platform, such as Zoom. Participants who meet eligibility criteria are scheduled for a virtual enrollment session during which study staff obtain informed consent using electronic consent procedures. Caregivers are only eligible to enroll if their corresponding TGD young adult has already been enrolled. During the enrollment process, the TGD young adult identifies one primary caregiver to be invited. This ensures that caregiver participation is directly linked by study staff to the corresponding TGD young adult enrollment, preserving the integrity of the dyadic intervention model.

Prior to the start of any study procedures, research staff conduct a comprehensive informed consent process. Participants are informed about the expected length of the session and advised to join from a quiet, private space with a reliable internet or phone connection. Participants are provided a copy of the informed consent form in advance or at the start of the session. A link to the informed consent form in REDCap is sent, and the document is reviewed together during the Zoom call.

Throughout the consent process, staff pause at the end of each major section to summarize key points and check for understanding. Participants are encouraged to ask questions, and staff conduct a verbal comprehension assessment by asking participants to explain back the information they have heard. These checks are repeated after key sections—particularly those on study procedures and risks—and again before signing the form. Any unclear points are rephrased to ensure clarity. Once all questions have been addressed, participants complete the electronic consent form by entering their initials and signature in REDCap. A copy of the signed document is then provided to the participant for their records.

### Intervention Allocation and Randomization

Randomization occurs following completion of the enrollment visit. Participants are randomized in a 1:1 ratio to either the immediate intervention arm or the deferred arm (6-month waitlist control). TGD young adults and their caregivers who enroll as dyads are randomized together as a unit to maintain the dyadic structure of the intervention.

Randomization is conducted using an automated, computer-generated sequence within REDCap. The allocation sequence is concealed, and blinding is maintained at the analyst and investigator levels to reduce bias. Once randomization is complete, study staff notify participants of their group assignment using the participant’s preferred method of contact (eg, email or phone).

Regardless of assignment, all participants receive a curated list of national and state mental health support resources.

### Intervention Delivery

TGD young adults and caregivers assigned to the immediate intervention arm receive full access to the digital app. After informed consent is obtained, participants are emailed a personalized link to download the app and complete registration. Only enrolled participants are able to create an account and access the app content. Participants randomized to the deferred arm also receive immediate access to the app; however, they are initially limited to viewing the Community Resources tab, which includes local, regional, and national resources. All other features are automatically unlocked after 6 months.

The intervention supports dyadic participation, with approximately one-third of TGD young adults expected to participate alongside a caregiver. With mutual consent, TGD young adults and caregivers may choose to link their accounts. All linking is reviewed and performed manually by study staff to ensure participant privacy and data integrity.

For dyads, accounts are manually linked by research staff once both participants have downloaded the app and completed registration. If linking is requested after enrollment, the app includes a feature that allows both participants to independently provide consent for linking. Once consent is confirmed, the study team is notified, and accounts are linked manually. Linking allows for shared activities and progress tracking but is entirely optional. Participants may request to unlink their accounts at any time, and study staff will promptly honor the request. This option, along with the voluntary nature of linking, is clearly communicated during the consent process and outlined in study documentation.

### Measures

#### Self-Reported Surveys

Online self-reported survey assessments are administered at baseline, 6 months, and 12 months (see Figure 1). Both TGD young adults and caregivers complete overlapping and complementary measures. Whenever possible, validated instruments—particularly those previously used with TGD and caregiver populations—were selected to ensure methodological rigor and comparability with existing research. All measures were pilot tested prior to implementation.

A computer-assisted self-interview is used to ensure consistency in data capture (eg, skip patterns and logic checks) and to reduce social desirability bias. Surveys are designed to take approximately 30 minutes to complete.

Survey domains include sociodemographic characteristics (age, race, ethnicity, gender identity, sexual orientation, socioeconomic status, religious affiliation, family composition, urbanicity, and nativity) [36]. Health care access and engagement includes general physical and mental health in the past month [37], health insurance coverage, access to primary care, unmet medical and mental health needs, and use of mental health services (inpatient, outpatient, medications, and support groups). Gender transition and journey includes age of first TGD recognition, types of gender affirmation (social, medical, legal), and family or peer disclosure and support. Family relationships are assessed via validated measures including family communication and satisfaction (Family Adaptability and Cohesion Scale III and IV) [38,39], family acceptance, and family empowerment [40]. Community belonging is measured using the Community Connectedness subscale of the Gender Minority Stress and Resilience Measure [29]. Mental health outcomes include suicidal ideation and attempts (lifetime and past 3 months) using the Columbia Suicide Severity Rating Scale (C-SSRS) [41], nonsuicidal self-injury using the SOARS (Suicidal ideation; Onset, frequency, and methods; Aftercare; Reasons; Stage of change screening and assessment of nonsuicidal self-injury) [42], depressive symptoms using the Patient Health Questionnaire-9 [43], anxiety symptoms using the Generalized Anxiety Disorder-2 [44], gender euphoria (3 items developed from qualitative research) [45], gender dysphoria via the Gender Preoccupation and Stability Questionnaire-2 [46], and substance use risk via the CRAFFT (Car, Relax, Alone, Forget, Friends, Trouble) screener [47]. Psychosocial context includes validated assessments of perceived stress [48], resilience [49], perceived social support [50], social safety [51], and perceived impact of legislative climate [52]. Social context and behavior includes bullying and social media use via questions adapted from the Youth Risk Behavior Surveillance System [53] and civic engagement using the Social Justice Scale [54]. Intervention engagement includes app engagement, acceptability [55,56], and the Net Promoter Score [57]. Caregivers complete additional assessments including the Transgender Knowledge, Attitudes, and Beliefs Scale [58]. TGD young adult-caregiver dyads complete 6 items from the Child-Parent Relationship Scale to assess the perceived impact of joint participation [59].

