**Figure 1 figure1:**
[figure not shown]
TransHealthGUIDE (Transforming Mental Health for Transgender and Gender-Diverse Young Adults Using Interventions to Drive Equity) study schema. Target sample size is 500 TGD young adults, with one-quarter (125 participants) in a dyad with a caregiver (target sample size of 125 caregivers). TGD: transgender, nonbinary, and gender diverse.

Participants in the immediate intervention arm receive full access to the TransHealthGUIDE digital app for the first 6 months. This is followed by a 6-month observation period during which they retain access to the app but receive no new intervention content or engagement prompts. Participants in the deferred intervention arm receive limited access to the app for the first 6 months, consisting primarily of curated local, regional, and national support resources. At the 6-month mark, participants in the deferred arm are granted full access to the digital app for the remainder of their participation.

Survey assessments are administered at baseline, 6 months, and 12 months to evaluate primary outcomes (past 3-month suicidal ideation and past 2-week depressive distress) as well as secondary measures.

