### Remuneration

Participants receive a US $25 e-gift card after completing each survey at baseline, 3 months, 6 months, and 12 months, along with a US $25 bonus for completing all surveys, for a total of US $125. Payments are sent via an e-gift card to the participant’s email after each survey is completed.

An e-gift card was chosen as the compensation method due to the remote nature of participant interactions. The US $25 per survey completion amount is based on feedback from the CAB, which deemed this amount appropriate for the study’s context.

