### Ethical Considerations

Boston Children’s Hospital (BCH) is the prime grant awardee and serves as the primary site for study operations and implementation. The BCH Institutional Review Board (IRB) serves as the single IRB of record for the study (protocol approval number IRB-P00046532).

The University of Michigan School of Public Health, which houses the methodology and data analysis core, and Massachusetts General Hospital, which serves as the clinical psychiatry and mental health safety core, are designated as relying sites under the single IRB structure. The study is covered by a Certificate of Confidentiality from NIH.

A data safety and monitoring board has been established to oversee the trial’s progress, review safety data, and make recommendations regarding the continuation of the trial based on its evaluation of participant safety and the overall performance of the research.

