#### Primary Aim Analyses

The primary outcome is suicidal ideation in the past 3 months, assessed using the 6-item C-SSRS. The C-SSRS demonstrates strong validity, with 100% sensitivity and 99.4% specificity for identifying aborted suicide attempts, and 100% sensitivity and specificity for classifying interrupted and actual suicide attempts, when compared to clinician-administered instruments [41]. The secondary outcome is depressive distress over the past 2 weeks, measured using the Patient Health Questionnaire-9, where a score of ≥10 indicates a positive screen for symptoms of clinically elevated depressive symptoms (88% sensitivity and 88% specificity for detecting major depression) [43].

Before analysis, data will be audited for quality and completeness. Descriptive statistics—including counts, percentages, means, medians, standard deviations, and ranges—will summarize baseline characteristics. Group differences at baseline will be assessed using *t* tests for continuous variables and chi-square tests for categorical variables. Variables that differ significantly between study arms may be included as covariates in subsequent models. All analyses will be conducted using SAS or R statistical software.

To evaluate intervention effectiveness, we will use an intention-to-treat approach. Poisson generalized estimating equations with a log link function will estimate the population-average (marginal) effect of the intervention on suicidal ideation from baseline to 6 months postrandomization [60]. An unstructured correlation structure will be used to account for within-subject correlations across repeated measures (baseline, 3 months, and 6 months).

The primary endpoint analysis will compare the proportion of participants reporting suicidal ideation in the past 3 months between the immediate and deferred (waitlist control) arms. The model will include a common intercept and fixed effects for the intervention arm (immediate vs deferred) and time point (3 vs 6 months). Baseline characteristics that differ significantly between groups and variables related to missingness will be included as covariates, if appropriate.

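### The past-3-month suicide-attempt item does not reach months 6-9 on either stated survey schedule, nor months 0-3 if no month-3 survey is run

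*Protocol article*

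**What the plan says.** Under Measures, Self-Reported Surveys, the mental health outcomes include "suicidal ideation and attempts (lifetime and past 3 months) using the Columbia Suicide Severity Rating Scale (C-SSRS". Two windows are given, and neither runs back to the previous survey.

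The survey schedule is stated in two ways.

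- **Three surveys.** Self-Reported Surveys says "Online self-reported survey assessments are administered at baseline, 6 months, and 12 months (see Figure 1". Study Design agrees: "Survey assessments are administered at baseline, 6 months, and 12 months to evaluate primary outcomes". The abstract gives the same three time points.
- **Four surveys.** Remuneration pays participants "after completing each survey at baseline, 3 months, 6 months, and 12 months". Primary Aim Analyses models "within-subject correlations across repeated measures (baseline, 3 months, and 6 months", and Secondary Aims Analysis uses mediators at month 3.

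On app access, Study Design says "Participants in the immediate intervention arm receive full access to the TransHealthGUIDE digital app for the first 6 months"; that arm then has six months of observation with access retained. For the other arm, "At the 6-month mark, participants in the deferred arm are granted full access to the digital app for the remainder of their participation"; before that it sees mainly the community resources.

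Under Ethical Considerations, a data safety and monitoring board is to "review safety data, and make recommendations regarding the continuation of the trial based on its evaluation of participant safety". Primary Aim Analyses defines the primary outcome as suicidal ideation in the past 3 months. The article describes no analysis of attempts.

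**The concern.** A 3-month look-back cannot bridge a 6-month interval between surveys. Any such interval leaves its first three months outside the item, and here those months follow a start of full access: month 0 in the immediate arm, month 6 in the deferred arm. The app includes modules on self-harm, coming out and family rejection, and may bring in a caregiver. It is therefore reasonable to want attempts ascertained in the same way, from everyone, when exposure begins.

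At stake is the completeness of the survey data on attempts, which the safety board may rely on and which any later account of harms would draw on. Analysis cannot recover an event that no question asked about.

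**Working it through.** **Inputs.** Look-back of 3 months (Self-Reported Surveys). Survey months 0, 6, 12 (Study Design, Self-Reported Surveys) or 0, 3, 6, 12 (Remuneration, and by implication the analysis sections). Full access from month 0 (immediate) or month 6 (deferred). Target of 500 young adults randomized 1:1, so 250 per arm.

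**Coverage rule.** A survey at month v with a 3-month look-back covers months v−3 to v. The baseline survey covers only time before randomization.

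| Schedule | Covered after baseline | Uncovered | Share of 12 months |
|---|---|---|---|
| 0, 6, 12 | 3-6, 9-12 | 0-3, 6-9 | 6/12 = 50% |
| 0, 3, 6, 12 | 0-3, 3-6, 9-12 | 6-9 | 3/12 = 25% |

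Months 6-9 are uncovered in both rows. Within months 0-6, the only period with a comparison against waitlist, the three-survey schedule leaves 3 of 6 months (50%) uncovered and the four-survey schedule leaves none.

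**How much of the gap is first full access?** Before attrition, in person-months:

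- Total follow-up: 500 × 12 = 6,000.
- Four surveys: uncovered 500 × 3 = 1,500 (25%). First full access is the deferred arm only: 250 × 3 = 750, half of the gap. The other 750 is immediate-arm observation.
- Three surveys: uncovered 500 × 6 = 3,000 (50%). First full access is 250 × 3 (immediate, months 0-3) + 250 × 3 (deferred, months 6-9) = 1,500, again half. The rest is deferred-arm waitlist time (months 0-3) and immediate-arm observation (months 6-9).

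**What a repeated lifetime item would add.** Take an attempt in a gap, with the lifetime item asked again at the next survey:

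- No attempt before: lifetime changes from no to yes while past-3-month stays no. The attempt is visible, with its timing bounded by the two surveys.
- An attempt before: lifetime is yes both times and past-3-month is no. The new attempt is invisible.

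If lifetime is asked only at baseline, neither case is visible. The article does not say which applies.

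**Which schedule is likelier?** The remuneration total is $125. Four surveys plus the bonus give 4 × $25 + $25 = $125; three would give 3 × $25 + $25 = $100. The payment text therefore fits four surveys, but three other places in the article state three.

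**Check of the remedy.** If the window runs back to the previous survey, it spans 6 and 6 months on the three-survey schedule, or 3, 3 and 6 months on the four-survey schedule. Each sums to 12 with no gap.

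**The case against.** The strongest reply is that nothing in the planned efficacy analysis is wrong. The C-SSRS is listed among mental health outcomes, not as the trial's safety instrument. The primary outcome is ideation over three months, which the window fits by definition. Attempts are not a stated endpoint. If the month-3 survey is run, the whole randomized comparison is covered in both arms, and the gap falls only after the waitlist arm has crossed over. All of this stands, and it limits the point to ascertainment of attempts.

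It also rules out several stronger readings that a reader might infer:

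- *Attempts in the gaps are simply lost.* This does not follow: a repeated lifetime item would still show first-ever attempts.
- *The whole gap is early exposure.* Months 6-9 are first full access in the deferred arm only, and about half of the uncovered person-time is something else.
- *Half of follow-up is unobserved.* That holds only for the past-3-month item and only if there is no month-3 survey, which the article leaves contradictory.
- *A given number of attempts will be missed.* The article states no attempt rate, so any count would rest on an assumed one.
- *The safety board will be blind to early harm.* The article mentions a separate safety plan and does not list the board's data sources. Adverse-event reporting is commonly set out in a full protocol, which is not shown here. Nor does the article show that harm is likeliest early.

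What survives is narrow. The window and the survey dates are both stated, and they do not meet. Spontaneous reports, if collected, would not replace asking all participants in both arms the same question.

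**Conclusion.** The point holds as a low-cost improvement to harms ascertainment, not as an error in the primary analysis. On either schedule the past-3-month attempt item leaves months 6-9 uncovered (3 of 12 months); without a month-3 survey it also leaves months 0-3 uncovered (6 of 12 months in total). These fractions need no assumed event rate.

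The consequence depends on two things the article leaves open: whether the lifetime item is repeated, and whether the month-3 survey exists. If lifetime is repeated, the surveys lose repeat attempts and exact timing. If it is not, they lose every attempt in a gap. The conclusion concerns survey data only and makes no claim about event reporting described elsewhere.

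**What to change.** - Keep the past-3-month C-SSRS item unchanged for the primary outcome.
- At each post-baseline survey more than 3 months after the previous one, add a suicide-attempt item worded 'since your last study survey', with approximate month. That means month 12 in every case, and month 6 if there is no month-3 survey.
- Tabulate the item by arm and by full-access status in the safety board's reports.
- Reconcile the two survey schedules throughout the article, and state whether the lifetime item is repeated at follow-up.

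The cost is about a minute of survey time, a REDCap change and a short amendment, with no extra visits. The downside is somewhat longer recall for this one item. At the article's cutoff of May 2, 2025, enrollment visits had begun nine days earlier (April 23) and five young adults were enrolled. No follow-up survey was yet due, so a change made then would have covered everyone.

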#### Digital App Usage and Metadata

Digital app usage and metadata information are collected and linked to participants’ survey responses to assess engagement and evaluate the intervention’s impact over time. This linkage enables a nuanced analysis of trends across the study period. The following types of app engagement data are collected: module engagement (number of educational modules completed), interactive features (frequency of engagement with interactive features such as posting, reacting or liking, and responding to posts), time spent (total time spent in the app and within specific modules), dyadic participation (dyad status, frequency of interactions between linked TGD young adult-caregiver pairs), goal-setting feature (usage and frequency of interaction with the goal setting component), log-in frequency (number of log-ins to the app), and technical issues (reports of technical difficulties or user-reported problems.) These metrics support the interpretation of intervention exposure and user experience, and inform potential improvements to future iterations of the app.

